**Fig. 1 Fig1:**
[figure not shown]
Flow Diagram

An effect size of 0.22 corresponds to a change of 5 min/day in moderate/vigorous PA (within-cell SD = 11) and a change of 5.4 min/day of sedentary time (within-cell SD = 12) [44].

Statistical analysis will be conducted on an intention-to-treat principle. Therefore, all children will be included in the analysis regardless of the intervention uptake. However, the percentage of “attendance” (compliance) of each child/family can be measured and will be used for subsequent analyses to evaluate the intervention uptake by the families.

Baseline characteristics will be described using summary measures and mixed models (with school as random effect), selected depending on their distribution. The effect of the two interventions on each one of the study outcomes will be estimated using a generalized mixed linear model with link and distribution selected according to the type of outcome. The model will include “active breaks” (AB), “virtual” (V), active breaks and virtual (AB + V), time (baseline/end of study) and the interactions time*AB, time*V and time*AB + V as fixed effect. It will also include random effects: child (or mother) to account for the repeated measures, and school to account for the cluster induced by the school. The most parsimonious model for each outcome will be reported. The False Discovery Rate criterion will be used to correct for multiple testing in non-planned analyses.

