**Methods:**

This is cluster-randomized controlled trial designed to run from July 2015 to November 2016 in 12 public schools of the city of Buenos Aires, matched for socio-demographic characteristics. The intervention is based on two main components: (a) “active breaks” (AB): implemented during school breaks by a PA instructor; (b) “virtual” (V): web-based contents delivered to the families via a multiplatform application. Using a computer generated random sequence participants are allocated to one of four intervention conditions: (AB), (V), (AB + V), and control (C). Outcomes are measured at baseline and 12 months post intervention, and will include data collected from the child and her/his mother/father or guardian. Primary outcome measures are: PA and sedentary behaviour (measured with accelerometers). Secondary outcome measures related are: percentage of kilocalories (kcal) from added sugars, and from total and saturated fats; grams of fruits and vegetables; and number of snacks and kcal coming from their added sugars and total and saturated fats. Family socio-economic level, home environment, and school environment will also be assessed. Statistical analysis is on an intention-to-treat principle. Baseline characteristics are described using summary measures and mixed models (with school as random effect). The effect of the two interventions will be estimated using a generalized mixed linear model with link and distribution selected according to the type of outcome. Included random effects are: child (or mother/father or guardian) accounting for repeated measures; school accounting for cluster induced by school. The most parsimonious model for each outcome will be reported. The False Discovery Rate criterion will be used to correct for multiple testing in non-planned analyses.

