### Study design

This is a cluster-randomized trial with four arms defined by a factorial structure of the two components of the intervention: the school-based (active breaks) (yes/no); family-based (web-based or virtual) (yes/no). The four arms of the study are: Active Breaks (AB) intervention, Virtual intervention (V), Active Breaks and Virtual intervention (AB + V) and neither AB nor V, control (C). The unit of randomisation is the school (rather than individual children/families). The study will run during two school semesters along two calendar years (the second semester of first grade and first semester of second grade). Because the enrolment process of families in the study lasted approximately 3 months, the study ran from July 2015 to November 2016.

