### Study population and randomization

The Ministry of Education of the city of Buenos Aires pre-selected a pool of public schools, which were invited to participate. Written invitations and an information pack were sent to each school Principal, followed up with visits to recruit schools. Consent was sought from Principals and first grade teachers. The 12 participating schools are located in middle-to low-income areas of the city. The schools were randomly allocated to one of the four intervention conditions using a computer generated random sequence. Blinding was not possible due to the characteristics of the intervention.

While part of the intervention is school-based, the primary outcomes are measured at subject level. Subjects of the study are first grade children. Mothers are also being assessed to evaluate parental factors; the dyad comprised the child and either parent or guardian in case the mother can’t attend the interview. All parents of first grade students (typically aged 6) of participating schools were invited to attend a meeting in which the nutritionist presented the program and described the study as well as the type of participation expected from parents and children. Those expressing interest were invited to enrol in the study and an initial face-to-face interview to be held at school was scheduled. Dyads were excluded if the child had severe intellectual difficulties or limitations to engage in physical activity, suffered from illnesses compromising nutrition or food selection, was taking medication known to affect body weight; or if the participating adult had severe intellectual difficulties. After screening for eligibility, the interviewer briefly explained the purpose and characteristics of the program and those who agreed to participate signed the informed consent form. Because the study is web-based, families without Internet access (at home, work or in the neighbourhood) are discouraged from participating. Should they still express wish to participate their data is collected but will be excluded from the analysis. Dyads attending a given school were assigned to the intervention condition randomly allocated to that school.

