### Data collection

Due to logistic reasons the participating schools will be join the program in a series of steps. The first assessment interview (baseline) will take place sometime between June and October 2015. The second assessment interview (at the end of the intervention) will take place 12 months later. In the few cases where the adult participant of the dyad is different from the mother (typically a father), he will not be included in the anthropometric assessment.

Data will be be collected via questionnaires and objective measurements. The child is only subject to the latter; only the mother will respond to the former. The questionnaires will be administered in face-to-face interviews with the participating mother. After ending the baseline interview, mothers will receive instructions regarding the use of the accelerometer with a diary to be filled out by the mother during the 7 consecutive days of use. Eight days later, a research assistant will retrieve the child’s accelerometer at school.

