### Statistical considerations

Sample size and power calculations. The number of children enrolled in first grade in the 12 participating schools is 405 [(range: 11–55, mean = 35]. Assuming approximately 50% participation rate the aim is to enrol a minimum of 200 dyads, i.e. 50 per trial arm. Assuming an additional 20% attrition it is expected to collect data on 160 dyads (40 per arm, an average of 13 per school) (Fig. 1). Under a factorial ANOVA design with two factors (V and AB interventions), and each at two levels, the target sample size of *N* = 160 participants (40 in each of the four conditions) yields a 80% power to detect an effect size of 0.22 (Cohen’s f low/moderate) for any of the main effects (V, AB) and the interaction effect (V*AB); F test, α = 0.05.

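### The school random effect, read as constant over time, drops out of the time-by-intervention effects, so the primary tests would ignore any difference between schools in change

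*Protocol article*

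**What the plan says.** All references are to the protocol article.

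- **Randomisation** (Study design): "The unit of randomisation is the school (rather than individual children/families".
- **Number of schools** (Study population and randomization): 12, allocated to four arms of a 2 x 2 factorial.
- **Analysed sample** (Statistical considerations): after dropout, "it is expected to collect data on 160 dyads (40 per arm, an average of 13 per school".
- **Effects of interest** (Statistical considerations, analysis paragraph): besides the intervention terms, the fixed part has "time (baseline/end of study) and the interactions time*AB, time*V and time*AB + V as fixed effect". Outcomes are taken at baseline and 12 months, so these interactions are differences in change.
- **Random part** (same paragraph): "random effects: child (or mother) to account for the repeated measures, and school to account for the cluster induced by the school". The Abstract repeats it: "school accounting for cluster induced by school".
- **Model reduction**: the same paragraph says that only the simplest adequate model will be reported for each outcome, with no exemption for the cluster terms.

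No school-by-time effect, random school slope, cluster-robust variance, school-level analysis or degrees-of-freedom method is mentioned.

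**The concern.** The article claims that the school term takes care of the clustering. A school effect that is the same at both waves handles clustering of levels: children of one school being more or less active throughout. The intervention effects are contrasts of change, and the relevant clustering there is that children of one school may change together. A time-constant school effect cannot represent that.

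Shared change is plausible from the article's own text. In The intervention section, the daily amount of active play depends on the school, use of the materials in PA class depends on the teacher's willingness, and the number of delivered days varies with closures and instructor availability. Children of a school also move from first to second grade together between the waves.

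At stake are the standard errors, p-values and intervals for moderate-to-vigorous PA and sedentary time. If the schools split equally there are three per arm, so one or two schools with an unusual change could produce an apparent intervention effect. Correcting the sample size would not cure this, because the analysis would still use the wrong error term.

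**Working it through.** **Inputs from the article.** 12 schools, four arms; 160 analysed children, so m = 160/12 = 13.33 per school; two waves; f = 0.22, alpha 0.05, stated power 80%; 20% attrition. **Assumed, because not given:** the intra-school correlation of change, rho, from 0 to 0.10.

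**1. The plan's own figure.** Individual-level factorial ANOVA: noncentrality = 0.22² x 160 = 7.744 with 1 and 160 - 4 = 156 df gives power 79.0%, which reproduces the stated 80% within rounding. The calculation treats the 160 children as independent.

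**2. Cancellation.** Write Y_ijt = fixed part + school_j + child_ij + e_ijt, with t = 0, 1. Then Y_ij1 - Y_ij0 = fixed change + (e_ij1 - e_ij0). Both random effects are gone.

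Numerical check with 12 schools x 13 children = 156, and child and residual variance both 60 (assumed). The variance of a child's change is 2 x 60 = 120. For AB against no AB (78 v 78), SE = sqrt(120 x (1/78 + 1/78)) = 1.754. Generalised least squares under the plan's model gives this same 1.754 with the school variance set to 0, 10, 50 or 1000. With 20% of follow-ups missing, the SE moves only from 1.911 to 1.912 over that range.

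**3. What the model leaves out.** Let s be the school-by-time variance per wave. The true SE is sqrt(3.077 + 2s x (1/6 + 1/6)), where 3.077 = 1.754²:

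- s = 1: sqrt(3.744) = 1.93
- s = 2: sqrt(4.410) = 2.10
- s = 5: sqrt(6.410) = 2.53

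These correspond to rho = 2s/(2s + 120) = 0.016, 0.032 and 0.077. The model as written has no term for s.

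**4. Size for the planned trial.** Design effect DE = 1 + (13.33 - 1) x rho. The SE is understated by the factor sqrt(DE). Approximate type I error = 2 x P(t156 > 1.975/sqrt(DE)). The simulated column gives the rejection rate of the child-level change test under no effect (20,000 runs per setting).

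| rho | DE | Interval too narrow by, from the SE alone (1 - 1/sqrt(DE)) | Type I error, formula | Type I error, simulated |
|---|---|---|---|---|
| 0 | 1.00 | 0% | 5.0% | 5.1% |
| 0.01 | 1.12 | 6% | 6.4% | 6.3% |
| 0.02 | 1.25 | 10% | 7.9% | 7.8% |
| 0.05 | 1.62 | 21% | 12.2% | 12.8% |
| 0.10 | 2.23 | 33% | 18.8% | 19.5% |

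A separate simulation gave 4.8%, 6.5%, 7.9%, 12.3% and 19.3%. A school-level test on 12 - 4 = 8 df stayed at 4.8% to 5.3%. Fitting the plan's mixed model directly at rho = 0.05 rejected in 15.3% of 300 runs. That figure is rougher (Monte Carlo error about ±4 points, some convergence warnings) but agrees.

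**5. After correction.** On 8 df the critical value is 2.306 instead of 1.975. The correct interval is sqrt(DE) x 2.306/1.975 times as wide as the child-level one: 1.17, 1.24, 1.30, 1.48 and 1.75 for rho = 0, 0.01, 0.02, 0.05 and 0.10. Power at f = 0.22 (noncentrality 7.744/DE, 1 and 8 df) is 68.5%, 63.5%, 59.0%, 48.6% and 37.5%.

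**The case against.** The strongest reply is that the premise is inferred. The article does not call the school effect an intercept, and a full protocol or SAP might let it vary with time. But the article lists the random effects and says what the school term achieves. It writes out time interactions for the fixed effects and for none of the random ones. The plain reading is a constant effect, and the stated rule does not do what is claimed for it.

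Several stronger readings are tempting but not supported:

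- **That intervals are certainly too narrow.** This holds only if schools differ in change. At zero correlation the test keeps its 5%, and the documents give no value. The 12% to 20% error rates need assumed correlations of 0.05 to 0.10.
- **That all secondary outcomes are hit equally.** The link depends on the outcome, and the number of snacks is a count. With a non-identity link the cancellation is only approximate.
- **That staged entry creates shared seasonal change.** Data collection says the "participating schools will be join the program in a series of steps", but the second assessment follows 12 months after the first, so a stable seasonal effect largely cancels too. Only year-specific events remain.
- **That delivery differences apply to both components.** The PA instructors rotate among schools, which reduces instructor effects, and the virtual content is viewed by individual families. The delivery argument is mainly about active breaks.
- **That the plan tests on 156 df.** No method is named for the mixed model. The figure is implied by the sample-size ANOVA.

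**Conclusion.** The point holds in conditional form. For the two primary outcomes, a time-constant school effect gives the time-by-intervention tests essentially no protection against clustering of change, contrary to what the analysis paragraph and the Abstract say. If schools differ in change, type I error exceeds 5%: about 6%, 8%, 12-13% and 19-20% at rho = 0.01, 0.02, 0.05 and 0.10. At rho = 0 there is no inflation.

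This rests on the plain reading of the random effects, an identity link, about 13 children per school and an assumed range for rho. The algebra is certain; the size is not. It should still be corrected before analysis: primary inference in a trial of 12 randomised schools should not depend on the untested assumption that schools do not differ in change, and the model as written has no term that could reveal such a difference.

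**What to change.** In the analysis paragraph of Statistical considerations and in the Abstract:

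1. Add a random school-by-time effect to the school and child effects.
2. Exempt it from the reduction to the simplest model, so that it stays whatever its estimated variance.
3. Base inference for the intervention effects on school-level degrees of freedom, for example by Kenward-Roger or Satterthwaite for Gaussian outcomes. The design supplies 12 - 4 = 8. The Abstract calls the schools matched; if matching was used in the allocation, there are fewer, and the text should say so.

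Two equivalents would serve: an analysis of the 12 school mean changes, or a model of the 12-month value adjusted for baseline with a school random intercept.

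The cost is a sentence or two and one variance component, with no new data. The downside is wider intervals and lower power than the individual-level calculation implies (68.5% at rho = 0 and 48.6% at rho = 0.05, against the stated 80%).

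### The stated mixed model tests differences in change but has no school-by-time random effect, so if schools differ in change the intervals are too narrow and type I error exceeds 5%

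*Protocol article*

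**What the plan says.** The trial randomises schools. Under Study design: "The unit of randomisation is the school (rather than individual children/families". Under Study population and randomization, 12 schools are divided among four arms: "The schools were randomly allocated to one of the four intervention conditions using a computer generated random sequence".

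The model is written out in Statistical considerations, in the text after Fig. 1. Its fixed effects are the three intervention terms, time at two points (baseline and end of study), and "the interactions time*AB, time*V and time*AB + V as fixed effect". Its random part is "random effects: child (or mother) to account for the repeated measures", together with "school to account for the cluster induced by the school". The Methods part of the abstract lists the same two random effects, the second as "school accounting for cluster induced by school".

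No section names a random school-by-time effect, a school-level slope for time or a degrees-of-freedom method. The same section says that the most parsimonious model will be reported for each outcome. The planned analysis set is "160 dyads (40 per arm, an average of 13 per school").

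**The concern.** With one baseline and one follow-up measurement, the intervention effect is a difference in change, carried by the time interactions. A school effect that is constant over time is subtracted out of every child's change. The school term therefore protects comparisons of level, but not the comparisons on which the trial's conclusions rest. Children in a school that moves up or down as a whole over the year are treated as independent evidence about change.

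Some school-level variation in change is plausible on the document's own description. Follow-up crosses from first to second grade (Study design), which could move whole schools even if neither intervention works. Active-break time depends on the school and on days lost to closures (The intervention), and playground space varies (Background). These delivery differences matter mainly for the width of the interval around a real effect. Both primary outcomes, moderate to vigorous activity and sedentary time, are affected.

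**Working it through.** **1. The plan's own figure.** Inputs from Statistical considerations: N = 160, f = 0.22, α = 0.05, 2×2 factorial F test with 1 numerator df. The noncentrality is 0.22² × 160 = 7.744. On 1 and 156 df the power is 0.790, against the stated 80% (exact N for 80% is about 164). The stated differences agree with f: 5/11/2 = 0.227 and 5.4/12/2 = 0.225. The figure reproduces as a calculation for independent children.

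**2. What the stated model tests.** Write child i in school j at time t as fixed part + u_j + c_ij + e_ijt. The change is y_ij1 − y_ij0 = fixed part + (e_ij1 − e_ij0); both u_j and c_ij drop out. The model with school and child random intercepts was fitted to four simulated complete data sets. The time*AB estimate was identical to that from ordinary least squares on child change scores, and the standard errors agreed to about five decimals (for example 0.14879 by both routes).

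**3. Effect of school-level variation in change.** Let ρ be the ICC of change and m = 160/12 = 13.3. The true variance is the model variance times DE = 1 + (m − 1)ρ. With the large-sample critical value, the type I error is 2 × (1 − Φ(1.96/√DE)).

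Example at ρ = 0.05: DE = 1 + 12.33 × 0.05 = 1.617; 1.96/√1.617 = 1.541; type I error 0.123. The correct standard error is √1.617 = 1.27 times the reported one.

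**4. Results over an assumed range of ρ.** Simulations used 20,000 runs per setting under the null, with 12 schools, 3 per arm, and child-level degrees of freedom. Enrolment in Statistical considerations ranges from 11 to 55 per school, so unequal sizes (4, 14 and 22 analysed children in the three schools of each arm, illustrative) were also run.

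| ρ | DE | Type I, formula | Simulated, about 13 per school | Simulated, unequal schools | Power at f = 0.22 on 8 df |
|---|---|---|---|---|---|
| 0 | 1.000 | 0.050 | 0.049 | 0.050 | 0.69 |
| 0.01 | 1.123 | 0.064 | 0.062 | 0.069 | 0.64 |
| 0.02 | 1.247 | 0.079 | 0.081 | 0.089 | 0.59 |
| 0.05 | 1.617 | 0.123 | 0.126 | 0.150 | 0.49 |
| 0.10 | 2.233 | 0.190 | 0.197 | 0.236 | 0.38 |

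**5. A test that keeps school variation in the error term.** Analysing school mean changes on 12 − 4 = 8 df gave simulated type I error of 0.046 to 0.051 with near-equal schools and 0.041 to 0.046 with unequal ones. The last column of the table is the power of such a test: noncentrality 7.744/DE on 1 and 8 df, with f applied to the change.

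**The case against.** The best defence is that the article names grouping factors and their purpose, not a covariance structure. Random intercepts are a reading of the text, and a fuller analysis plan could add a school-by-time term. That is fair as far as it goes. But the article sets out the random part twice, identically, and puts the intervention effects in the time interactions. As stated, the model does not do what the design requires, and the parsimony rule works against adding a variance term later.

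Four stronger readings are tempting, and the documents do not support them.

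- A reader might infer that type I error is inflated as a matter of fact. It is so only if schools differ in change. At ρ = 0 the test holds its level, and the documents give no ICC.
- A reader might infer that the plan prescribes some 150 child-level degrees of freedom. It states no method. That figure follows only from the usual fit of the model as read here.
- A reader might take the stepwise entry of schools as a source of seasonal drift. Data collection puts the second assessment 12 months after the first, so each school is re-measured at the same time of year.
- A reader might expect that using baseline as a covariate would pay for the lost precision, through the factor (1 + r)/2, with r the baseline–follow-up correlation. That factor ignores clustering. Take total variance 1, r = 0.5 and a stable school ICC of 0.10 (school 0.10, child 0.40, residual 0.50). Change scores give a school-mean variance of 2 × 0.50/13.3 = 0.075. Baseline adjustment, with within-school slope 0.40/0.90 = 0.444, gives (1 − 0.444)² × 0.10 + 0.90 × (1 − 0.444²)/13.3 = 0.031 + 0.054 = 0.085. The ratio is about 1.1, a loss, where the simple factor promises 0.75. Analysing only the 12-month value would also drop children without follow-up unless they are imputed; the plan expects 20% attrition and an intention-to-treat analysis.

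**Conclusion.** The point stands as a flaw in the stated model. On a plain reading, the tests that carry the trial's conclusions leave school-level variation in change out of the error term, in a trial that randomises 12 schools. If schools differ in change, intervals are too narrow and a nominal 5% test runs at about 6%, 8%, 12% and 19% for ρ of 0.01, 0.02, 0.05 and 0.10, somewhat more with unequal schools. If ρ is zero it runs at 5%. With only 12 schools, the data could not reliably show that ρ is zero.

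This rests on the assumed range for ρ, three schools per arm (consistent with 40 per arm and 13 per school, but not stated), main-effect random terms, and a test referred to a child-level or normal distribution. The equivalence with change scores was shown for complete two-wave data and a Gaussian outcome. It does not rest on any claim about what an unseen analysis plan contains.

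**What to change.** Keep the repeated-measures model, so that children without follow-up stay in the intention-to-treat analysis, and make three changes to its description:

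1. Add a random school-by-time effect beside the child and school effects.
2. Test the time-by-intervention terms with small-sample degrees of freedom based on schools (about 8, for example Kenward-Roger or Satterthwaite), or use a school-level permutation test that follows the actual allocation scheme.
3. State that the school-by-time term stays in the model whatever its estimate, and is exempt from the parsimony rule. With 12 schools the estimate can be zero by chance.

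This needs no new data. Its cost is wider intervals and less power than the stated 80% at f = 0.22: about 0.69 on 8 df with zero ICC of change, 0.59 at 0.02 and 0.38 at 0.10. The article should state that loss beside the existing power figure and should not rely on baseline adjustment to recover it.

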The efficacy of the intervention will be evaluated through outcomes measured on the children. Primary outcomes: (Aim 1 -PA): 1) Total time (minutes/day) of children’s moderate to vigorous PA and 2) Sedentary time (minutes/day). Secondary outcomes: (Aim 2 - Quality of diet): 1) Percentage of kilocalories (kcal) from added sugars, 2) Percentage of kcal from total fats and saturated fats, 3) Grams of fruits and vegetables, and 4) Number of snacks and kcal from total fats, saturated fats, and sugars coming from snacks. The 4 secondary outcomes will be measured by a 24-h recall, using the multiple pass method, applied to both mother and child and complemented with information regarding school breakfast and lunch in order to collect intake from an ordinary school day, covering both home and school.

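### Reporting the most parsimonious model for each outcome lets the data decide which AB and V effect is reported, with no exemption for the primary outcomes

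*Protocol article*

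**What the plan says.** All points below are in the protocol article.

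- **Model.** Statistical considerations states that "The effect of the two interventions on each one of the study outcomes will be estimated using a generalized mixed linear model". The fixed effects are AB, V, AB + V, "time (baseline/end of study) and the interactions time*AB, time*V and time*AB + V as fixed effect". The model also has "random effects: child (or mother) to account for the repeated measures, and school to account for the cluster induced by the school".
- **Reporting rule.** The same paragraph then states: "The most parsimonious model for each outcome will be reported". The Abstract (Methods) repeats it. Neither place gives a selection criterion, a list of terms that must stay, or an exemption.
- **Outcomes covered.** The model applies to every study outcome. That includes both primary outcomes, children's moderate-to-vigorous activity and sedentary time in minutes per day.
- **What was powered.** The sample-size paragraph plans tests of both main effects and of their interaction at α = 0.05.
- **Design and aim.** The school is the unit of randomisation, and there are 12 schools in four arms. The Discussion says the components will be assessed separately and together.

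**The concern.** The rule is a positive instruction about what is reported, and it is applied outcome by outcome. The full model has seven fixed terms and two random terms, and nothing says which of them a simpler model may lose.

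If the interaction is removed for one outcome and kept for another, the AB coefficient answers two different questions in the same results table. The ordinary standard error and p-value of the chosen model ignore that the data did the choosing. The stated aim of separating the components depends on these coefficients keeping one meaning. The school term, which represents the unit of randomisation, has no stated protection either.

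**Working it through.** **1. The plan's own figure.** For N = 160 and f = 0.22, the noncentrality is f²N = 0.22² × 160 = 7.744. On 1 and 156 degrees of freedom the power is 0.790, which agrees with the stated 80%. The stated differences also fit: 5/(2 × 11) = 0.227 and 5.4/(2 × 12) = 0.225. This calculation takes the three effects as fixed in advance; no model selection enters it.

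**2. What the AB coefficient means.** Assume 0/1 coding, with AB + V read as the interaction, and work with change from baseline. Let g be the true interaction.

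- Interaction kept: S = mean(AB) − mean(C), which estimates AB without V.
- Interaction dropped: M = ½[(mean(AB) − mean(C)) + (mean(AB+V) − mean(V))], which estimates AB without V plus g/2.

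The two targets agree only when g = 0.

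**3. Size, illustrated.** From the documents: SD 11, a 5 min/day difference, 12 schools and about 13 children per school. Assumed: three schools per arm (39 children per arm), intraclass correlation (ICC) 0, true AB 5, V 5 and g = −5, and the interaction dropped unless p<0.05 on school means (12 − 4 = 8 df).

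- SE of the interaction = 11√(4/39) = 3.52, so g/SE = −5/3.52 = −1.42.
- SE(S) = 11√(2/39) = 2.49, with target 5.
- SE(M) = 11√(1/39) = 1.76, with target 5 − 2.5 = 2.5.

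Simulation results:

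| Quantity | Result |
|---|---|
| Interaction kept | 24% |
| Mean reported AB effect | 3.57 min/day |
| Coverage of AB without V (5) by the reported interval | 82% |
| Coverage of the averaged effect (2.5), always estimated by M | 95.0% |
| Coverage of whichever effect the chosen model targets | 94.6% |
| Coverage when the true interaction is zero | 93.5% |

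M is uncorrelated with the interaction estimate, so reports from reduced models average 2.5. Reports from full models must then average (3.57 − 0.76 × 2.5)/0.24 = 7.0. A full-model report therefore overstates AB without V (7.0 against 5), and the mean of all reports, 3.57, equals neither target.

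**4. Dependence on the selection rule.** A second set-up uses change scores in four cells of 40, with a true AB-without-V effect of zero:

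| True interaction | Rule | Type I error, AB without V | Coverage |
|---|---|---|---|
| 0 | p<0.05 | 0.065 | 0.935 |
| 0 | AIC | 0.073 | 0.927 |
| 0.44 SD | p<0.05 | 0.225 | 0.775 |
| 0.44 SD | AIC | 0.171 | 0.829 |

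Keeping the full model gives 0.048 to 0.053 throughout. In the last two rows the averaged effect is not zero, so those rejections are false only for AB without V.

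**5. The school term.** Take the model as written, with school and child intercepts. Assume total variance 1, ICC 0.05, residual variance 0.5, 17 children per school (200/12 = 16.7) and 20% missing follow-up.

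| Term | SE, school kept | SE, school dropped |
|---|---|---|
| AB | 0.188 | 0.140 |
| time*AB | 0.1518 | 0.1519 |

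Dropping school makes the SE of AB about a quarter too small (0.140/0.188 = 0.74). It leaves time*AB almost unchanged, because a school intercept cancels from within-child change.

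**The case against.** **The rule may be spelled out elsewhere.** An article condenses, and model-building detail often sits in a full protocol or analysis plan that is not shown. That excuses the missing criterion. It does not excuse the rule: a plan that always reported the full model would contradict this sentence.

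**The random effects are said to be included.** This is true, and a reader could take the parsimony sentence to concern fixed effects only. But the article uses the same language of inclusion for the fixed effects, so inclusion alone cannot be what protects a term.

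**Main effects are unaffected in a balanced 2×2.** This objection largely stands. The sample-size paragraph speaks of main effects. An averaged effect is orthogonal to the interaction and keeps its 95% coverage if it is always the effect reported. The 82% figure counts only against AB without V. The defect is therefore mainly that the target is not fixed.

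**A stronger reading is tempting on clustering.** A reader might infer that dropping school raises the type I error of the treatment effect to about 9% overall, or to 12% to 20% in trials where it is dropped. Simulations give such figures at ICC 0.05 to 0.10, but only with between-school variance in change scores. The stated model has no school-by-time term, so under that variance its error would be about 12% at ICC 0.05 even with school kept. Those figures cannot be charged to the parsimony sentence.

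**Conclusion.** The point holds in a limited form. The article prescribes outcome-by-outcome reduction of the model, with no exemption for the primary outcomes and no protected term. The reported AB and V effects can therefore change meaning with the data, and nominal error rates and coverage are not assured.

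In the main illustration, coverage of AB without V falls from 95% to about 82%. With no true interaction the loss is small: coverage is about 93.5%, and type I error is 0.065 to 0.073. The interaction size, ICC, equal allocation, coding and selection rule are all assumptions, because the article gives none of them.

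Two wider conclusions are not supported. The primary p-values are not shown to be invalid in general, since coverage of whichever effect the chosen model targets stays near 95% in the main illustration. Loss of the school term is a real gap for main-effect or follow-up contrasts, but it hardly affects time*AB in the model as written.

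A reader might also see a fault in the statement that "The False Discovery Rate criterion will be used to correct for multiple testing in non-planned analyses". Leaving planned factorial tests unadjusted is a separate, disclosed and debatable choice, and it forms no part of this point.

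**What to change.** For the primary outcomes, replace the sentence in Statistical considerations and in the Abstract with a statement that:

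- the pre-specified factorial model is reported whatever the size or significance of its terms, with AB, V, AB*V, time, all their interactions with time, and the child and school random effects;
- the AB and V effects have one definition for every outcome, either averaged over the other component or in its absence;
- any reduced model is labelled a sensitivity or exploratory analysis.

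The change is to wording only. When the interaction is truly zero, some precision is given up, and the amount depends on the definition chosen. For the averaged effect in a balanced design it is about one degree of freedom. For the effect without the other component, the SE is 2.49 against 1.76 in the reduced model of the illustration, a factor of √2. The averaged definition matches the main effects for which the sample size was calculated.
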